## Abstract

**Background:**

Immunocompromised hosts (ICH) experience more breakthrough infections and worse clinical outcomes following infection with COVID-19 than immunocompetent people. Prophylactic monoclonal antibody therapies can be challenging to access, and escape variants emerge rapidly. Immunity conferred through vaccination remains a central prevention strategy for COVID-19. COVID-19 vaccines do not elicit optimal immunity in ICH but boosting, through additional doses of vaccine improves humoral and cellular immune responses. This trial aims to assess the immunogenicity and safety of different COVID-19 vaccine booster strategies against SARS-CoV-2 for ICH in Australia.

**Methods:**

Bringing optimised COVID-19 vaccine schedules to immunocompromised populations (BOOST-IC) is an adaptive randomised trial of one or two additional doses of COVID-19 vaccines 3 months apart in people living with HIV, solid organ transplant (SOT) recipients, or those who have haematological malignancies (chronic lymphocytic leukaemia, non-Hodgkin lymphoma or multiple myeloma). Key eligibility criteria include having received 3 to 7 doses of Australian Therapeutic Goods Administration (TGA)-approved COVID-19 vaccines at least 3 months earlier, and having not received SARS-CoV-2-specific monoclonal antibodies in the 3 months prior to receiving the study vaccine. The primary outcome is the geometric mean concentration of anti-spike SARS-CoV-2 immunoglobulin G (IgG) 28 days after the final dose of the study vaccine. Key secondary outcomes include anti-spike SARS-CoV-2 IgG titres and the proportion of people seroconverting 6 and 12 months after study vaccines, local and systemic reactions in the 7 days after vaccination, adverse events of special interest, COVID-19 infection, mortality and quality of life.

**Discussion:**

This study will enhance the understanding of COVID-19 vaccine responses in ICH, and enable the development of safe, and optimised vaccine schedules in people with HIV, SOT, or haematological malignancy.

**Trial registration:**

ClinicalTrials.gov NCT05556720. Registered on 23rd August 2022.

**Supplementary Information:**

The online version contains supplementary material available at 10.1186/s13063-024-08315-2.

## Introduction

### Background and rationale {6a}

The COVID-19 pandemic has had a disproportionate impact on the health, wellbeing, and care of immunocompromised hosts (ICH) [1]. Early evidence demonstrated that people living with HIV (PLWH), those with solid organ transplants (SOT) and patients with haematological malignancies are at least twice as likely to experience COVID-19-related hospitalisation, intensive care admission and death compared to the age and sex-matched population [2–5]. Hence, strategies to reduce the incidence of COVID-19 infection and prevent the associated complications in these groups, including vaccination, remain central to public health efforts [6].

The higher likelihood of complications experienced by ICH may be dependent on co-existing comorbidities and level of immunosuppression as both innate and adaptive immunity is required to control the viral replication. PLWH, who experience earlier onset and a higher burden of age-associated comorbidities compared with the general population [7], have been shown to have a small, but potentially clinically important reduction in seroconversion and neutralisation responses following COVID-19 vaccination [6]. Those with low CD4 counts were less likely to demonstrate seroconversion or neutralisation following a primary course of COVID-19 vaccination [6, 8]. Similarly, several clinical trials and observational studies have shown significantly reduced humoral responses to standard two-dose schedules of COVID-19 vaccines, and a higher incidence of breakthrough COVID-19 infections in SOT recipients [9–11]. Several factors have been associated with decreased COVID-19 immune responses in SOT recipients, including the net state of immunosuppression and time from transplantation; the immunosuppressive regimen, including the administration of mycophenolate mofetil and prior use of T cell depleting agents as induction therapies [12]; and previous infection with COVID-19 and other coronaviruses [13–16]. While people with haematological malignancies are a heterogenous group, they experience some of the poorest responses to vaccination [17]. The type of haematological malignancy and type and timing of chemotherapy relative to vaccination are key predictors of attenuated immunity, with B-lymphocyte depleting therapies, like anti-CD20 monoclonal antibodies and Bruton’s tyrosine kinase inhibitors having deleterious effects on humoral immunity [17–19].

International guidelines recommend additional doses of COVID-19 vaccines for ICH [19, 20] though recommendations vary regarding the number and frequency of booster doses. Although a growing body of evidence illustrates that additional doses of COVID-19 vaccines enhance humoral responses among ICH [21–23], but the optimal boosting strategies, including the number of doses and type of vaccine, remain unclear [24–26].

High-quality, randomised controlled clinical trials of different boosting strategies are therefore needed to optimise COVID-19 vaccination in ICH, to enhance protective immunity, while maintaining an acceptable safety profile.

### Objectives {7}

This study aims to assess humoral and cellular responses and confirm the safety of an additional one or two doses of an approved COVID-19 vaccine, 3 months apart, in PLWH, SOT recipients, and those with haematological malignancy. Specifically, we aim to examine how additional doses of COVID-19 vaccine/s affect the geometric mean concentration of anti-spike SARS-CoV-2 IgG antibody, 28 days after completion of the study vaccine, and other correlates of protective immunity.

### Trial design {8}

BOOST-IC is a multicentre, adaptive platform randomised trial, designed to compare up to three different vaccines at a given time. The design allows for the addition or removal of existing arms, in response to changes in recommendations from Australian authorities. This protocol is reported in keeping with the SPIRIT guideline [27].

## Methods: participants, interventions, and outcomes

### Study setting {9}

Eligible participants will be recruited in the outpatient setting at up to 16 academic hospitals in Australia (Appendix).

### Eligibility criteria {10}

Inclusion criteriaAble to give informed consent and undertake study proceduresAge ≥ 16 years oldHave completed 3 to 7 doses of Australian Therapeutic Goods Administration (TGA)-approved SARS-CoV-2 vaccine (including mRNA [Pfizer or Moderna], ChAdOx1 [Oxford/Astra Zeneca] or protein [Novavax]) at least 3 months priorFit the criteria to be included in one of the three following ICH groups:ο Infected with HIVο Recipient of a SOT including kidney, pancreas, liver, heart, lung, or combination of these organs at least 6 weeks prior and without episodes of severe rejection requiring T- or B-cell depleting agents in the prior 3 monthsο Undergoing chemotherapy, immunotherapy and/or targeted therapy, or completed in the last 2 years for chronic lymphocytic leukaemia (CLL), non-Hodgkin lymphoma (NHL), or multiple myeloma (MM).

Exclusion CriteriaContraindicated to receive a COVID-19 booster vaccine (e.g. history of anaphylaxis to a vaccine component or myocarditis attributed to previous receipt of an mRNA vaccine).Has had less than 3 or more than 7 doses of COVID-19 vaccineIs on another clinical trial investigating alternate COVID-19 vaccination schedules or investigational drugs to prevent or treat COVID-19Life expectancy < 12 months or enrolment deemed not in the best interest of the patientUnable to provide informed consentReceipt of SARS-CoV-2 specific monoclonal antibodies in the 3 months prior to receiving the first dose of study vaccineAcute respiratory tract infection and/or temperature > 38 degrees on the day of receipt of the first dose of the study vaccineHistory of autologous stem cell transplant in the prior 6 months or history of ever having an allogeneic stem cell transplant or CAR T-cell therapyHave not received another licensed vaccine in the 7 days before or plan to receive one in the 7 days after the day of receiving the COVID-19 study vaccine (note: participants can receive another licensed vaccine on the same day as the COVID-19 vaccine)

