### Relevant concomitant care permitted or prohibited during the trial {11d}

Participants should receive standard care throughout the study period. Participants may receive another licensed vaccine (e.g. influenza vaccine) in the opposite upper limb, concurrent with their trial vaccine. However, the other licensed vaccine cannot be administered in the period 7 days before or 7 days after the COVID-19 vaccine, to avoid misattribution of reactogenicity to the study vaccine.

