### Outcomes {12}

The primary outcome is defined as the geometric mean concentration (GMC) of anti-spike IgG antibody against SARS-CoV-2, 28 days after completion of trial vaccine/s, i.e. after one or two doses in the respective trial arms.

Secondary outcomes include laboratory, safety and clinical outcomes:

Laboratory outcomesThe GMC of anti-spike IgG antibody against SARS-CoV-2, 6 and 12 months after completion of trial vaccine/sThe proportion of participants seropositive to SARS-CoV-2 IgG, 1, 6 and 12 months after completion of trial vaccine/sThe GMC of anti-spike IgG antibody targeting specific SARS-CoV-2 variants, 1, 6 and 12 months after completion of trial vaccine/sThe SARS-CoV-2 neutralising antibody response, 1, 6 and 12 months post completion of trial vaccine/s, in a subset of participants with response defined as either rise in the neutralising antibody titreο Fourfold rise in the neutralising antibody titre for those with detectable neutralising antibodies at baseline, ORο Detectable neutralisation in those with no detectable neutralising antibodies at baselineThe magnitude of SARS-CoV-2 specific T-cell responses, 1, 6 and 12 months post completion of trial vaccine/s in a subset of participantsSubset analysis and polyfunctionality (number of effector cytokines) of SARS-CoV-2 specific T-cell responses, 1, 6 and 12 months post completion of trial vaccine/s in a subset of participants

Safety outcomesLocal and systemic reactions assessed on days 1, 2, 3, 4, 5, 6 and 7 after randomisation.Hospitalisation resulting from adverse events following immunisation (AEFI) up to day 28.Adverse events of special interest (AESI) up to 12 months post completion of trial vaccine/s

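### The last exclusion criterion has a stray negation: its look-back clause excludes people with no recent other vaccine and contradicts the concomitant-care rule

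*Protocol article*

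**What the plan says.** Eligibility criteria {10} of the protocol article gives the inclusion list first and then a separately headed exclusion list of nine items. The ninth covers people who have "not received another licensed vaccine in the 7 days before or plan to receive one in the 7 days after" the day of the COVID-19 study vaccine. A note to the same item adds that "participants can receive another licensed vaccine on the same day as the COVID-19 vaccine".

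Relevant concomitant care {11d} sets the rule for other vaccines during the trial. It allows co-administration: "Participants may receive another licensed vaccine (e.g. influenza vaccine) in the opposite upper limb, concurrent with their trial vaccine". It then closes the window on both sides: "the other licensed vaccine cannot be administered in the period 7 days before or 7 days after the COVID-19 vaccine". The reason given is "to avoid misattribution of reactogenicity to the study vaccine".

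The outcome which that reason protects is listed among the safety outcomes in Outcomes {12}: local and "systemic reactions assessed on days 1, 2, 3, 4, 5, 6 and 7 after randomisation". Adverse event reporting and harms {22} says the solicited events are collected by diary card for up to 7 days after each vaccination.

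**The concern.** An exclusion criterion describes a person who must not be enrolled. The other eight items do this; for example, one reads "Has had less than 3 or more than 7 doses of COVID-19" vaccine. The look-back half of the ninth item does the reverse. It states a condition that an eligible person should satisfy, as an inclusion criterion would. Under the exclusion heading it therefore bars the person the rule is meant to admit (no other vaccine in the preceding week) and admits the person it is meant to keep out.

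The look-forward half, "plan to receive one in the 7 days after the day of receiving the COVID-19 study vaccine", is a proper exclusion when read on its own and agrees with {11d}.

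What is at stake is attribution of reactions. Someone given another vaccine a few days before the study vaccine may report reactions to it in the study diary. The rule exists to prevent this, and the eligibility text gets that half of it backwards. A vaccine planned for the 7 days after is still barred.

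**Working it through.** No figure in the plan is involved, so the check is a logical comparison of the two sections.

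**Definitions**
- B = another licensed vaccine received in the 7 days before the study vaccine.
- A = another licensed vaccine planned for the 7 days after it.
- Same-day administration is permitted in both sections, so it counts as neither B nor A.

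**Rules**
- Relevant concomitant care {11d}: barred if B or A.
- Eligibility criteria {10}, ninth exclusion item: excluded if (not B) or A. Here the negation belongs to the verb of the first clause only. The second clause has its own verb, and carrying the negation across would be ungrammatical.

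**Comparison**

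| Vaccine before (B) | Planned after (A) | Exclusion item as written | Rule in {11d} | Result |
|---|---|---|---|---|
| No | No | Excluded | Permitted | Conflict |
| Yes | No | Admitted | Barred | Conflict |
| No | Yes | Excluded | Barred | Agree |
| Yes | Yes | Excluded | Barred | Agree |

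The conflicts number 2 of 4. Both have no vaccine planned after, so the look-back clause alone decides them. In the two rows that agree, the look-forward clause supplies the correct answer.

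**Does another reading remove the conflict?** Suppose the negation is carried over both clauses, so that the item describes people who neither had nor plan another vaccine. It then excludes if not (B or A), the exact complement of {11d}, and the conflicts rise to 4 of 4. Suppose instead that the sentence was meant as an inclusion criterion. Then it stands in the wrong list. The text needs correcting under each reading.

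**After correction.** With the negation removed, the item excludes if B or A. This is the same condition as in {11d}, so the conflicts are 0 of 4. The same-day exception is kept.

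**The case against.** The strongest objection is that nobody would apply the literal text. It would turn away everyone who had no other vaccine in the past week. {11d} states the true rule clearly and gives its reason, and the same-day note within the criterion makes sense only as an exception to a ban. Recruitment began in December 2022 (Trial status), and nothing in the document suggests that sites have misread the criterion. On this view it is a copy-editing slip, not a risk to participant selection. All of that stands, and it limits the size of the point. It does not make the criterion correct: an eligibility item is applied person by person and should not need another section to decode it.

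Two further points also limit the weight. The trial deliberately accepts same-day co-administration, which overlaps the diary week directly, so some uncertainty about which vaccine caused a reaction is built into the design. And this is a journal article condensed from protocol version 7.0, which is not shown, so the error may not be in the document the sites use. For that reason the full protocol should be checked and not assumed to be wrong.

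It can also be said that the count of two conflicts depends on how the sentence is parsed. It does, but the looser reading gives four conflicts, so the count used here is the more lenient one.

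**Conclusion.** The concern holds. The look-back clause of the ninth exclusion criterion is inverted and contradicts {11d}. On the grammatical reading, two of four exposure patterns are classified wrongly, including the pattern of a person with no other vaccine before or planned after, whom the rule is meant to admit.

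The size is minor. The outcome concerned is a secondary one, local and systemic reactions in the 7-day diary. No effect on the primary outcome, the sample size or the interim analyses is shown, and no difference between randomised arms is claimed. The number of participants affected cannot be derived from the document, and no misapplication is shown.

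The conclusion rests on two things: that the item belongs to the exclusion list under which it is printed, and that {11d} states the intended rule, which its stated purpose supports. It is a correction that should be made, because the text is an operative eligibility rule and the remedy is trivial.

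**What to change.** Reword the ninth exclusion item along these lines: *Has received another licensed vaccine in the 7 days before, or plans to receive one in the 7 days after, the day of receiving the COVID-19 study vaccine (same-day administration is permitted).*

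Then check that protocol version 7.0 and the eligibility checklist carry the correct wording. If they do, only the article needs correcting.

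The cost is one sentence and a document check. Design, data collection and analysis do not change.

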### Who will take informed consent? {26a}

Patients will only be included after providing written informed consent. Consent will be obtained by a member of the research team, who will ensure the participant is fully informed of the nature and objectives of the research, its voluntary nature, and any possible risks of participation, prior to data collection or the commencement of any study-related procedures. Where appropriate, accredited interpreters will be used to ensure the consent process occurs in the participant’s preferred language.

### Additional consent provisions for collection and use of participant data and biological specimens {26b}

All participants will provide consent to use deidentified data and blood specimens to determine the primary and secondary outcomes of the study. In addition, a subset of individuals can consent to provide additional blood samples for use in future research.

## Interventions

### Explanation for the choice of comparators {6b}

Vaccines for the prevention of COVID-19 infection and severe disease approved by the Australian TGA can be included in this trial. Candidate vaccines include mRNA and protein subunit vaccines. The choice of which vaccines to include in the platform is done by the trial steering committee and can change over time. Decisions on which vaccines to include in the trial are based on: availability, the current clinical environment including variants of concern, scientific merit and contemporary recommendations from the Australian Technical Advisory Group on Immunisation (ATAGI). This study does not include a placebo arm.

### Intervention description {11a}

At any one time, a minimum of 1 and a maximum of 3 vaccine candidates can be under investigation. At the time of writing, 2 vaccines are currently being studied in the trial. These are monovalent mRNA vaccines encoding XBB.1.5 Omicron spike proteins, manufactured by Pfizer and Moderna, and currently recommended as COVID-19 booster vaccines. These are associated with higher neutralising antibody titres to contemporary variants and have a comparable safety profile when compared with ancestral vaccines [28–37].

The vaccines used in this study have evolved in accordance with contemporary recommendations from ATAGI, and local vaccine availability. All randomised participants in receipt of current or past study vaccines will be included in the final analyses.

Vaccines previously used for participants enrolled in the trial but which are no longer included as a study intervention are:mRNA ancestral/Omicron BA.1 Bivalent (Pfizer)mRNA ancestral/Omicron BA.1 Bivalent (Moderna)mRNA ancestral/Omicron BA.4/5 Bivalent (Pfizer)mRNA ancestral/Omicron BA.4/5 Bivalent (Moderna)

All participants will receive either one or two doses of COVID-19 vaccine, prepared, stored and administered from multidose vials in accordance with the manufacturers’ instructions.

### Criteria for discontinuing or modifying allocated interventions {11b}

Participants may discontinue participation or withdraw their consent without penalty. An investigator may also discontinue a participant from trial intervention if the participant demonstrates significant non-compliance with the trial intervention; experiences a serious or intolerable adverse event such that continued trial intervention would not be in the best interest of the participant; or requires early discontinuation for any other reason.

### Strategies to improve adherence to interventions {11c}

Site investigators and trial coordinators will monitor the completion of safety questionnaires and contact participants if these are incomplete to see if any additional information or assistance is required to complete these tasks. Study site coordinators are educated to encourage attendance and contact participants missing any follow-up visits to maximise completeness of the study data. In addition, the study schedule allows for enrolment and the initial study vaccine on the same day to minimise study visits.

### Relevant concomitant care permitted or prohibited during the trial {11d}

Participants should receive standard care throughout the study period. Participants may receive another licensed vaccine (e.g. influenza vaccine) in the opposite upper limb, concurrent with their trial vaccine. However, the other licensed vaccine cannot be administered in the period 7 days before or 7 days after the COVID-19 vaccine, to avoid misattribution of reactogenicity to the study vaccine.

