**Fig. 1 Fig1:**
[figure not shown]
Trial design if **a**) one COVID-19 vaccine is included in the trial, **b**) if two COVID-19 vaccines are included in the trial, and **c**) if three COVID-19 vaccines are included in the trial

**Table 1 Tab1:** Schedule of activities

Protocol activities										
	**Visit 1**^**c**^ **Screening**	**Visit 2**^**c**^ **Baseline**	**Visit 3**	**Visit 4 **^**a**^	**Visit 5**^**a**^	**Visit 6**^**b**^	**Visit 7**^**a**^	**Visit 8**^**b**^	**Visit 9**^**a**^	**Unscheduled visit **^**f**^
Visit window	Up to 4 weeks pre M0	M0	M1 (D28) + / − 7 days	M3 (D84) + / − 7 days	M4 (D112) + / − 7 days	M6 (D180) + / − 30 days	M9 (D 270) + / − 30 days	M12 (D 365) + / − 30 days	M15 (D455) + / − 30 days	
Informed consent	✓									
Medical history, incl/excl criteria	✓									
Symptoms, adverse events,		✓	✓	✓	✓	✓	✓	✓	✓	✓
QOL		✓	✓		✓	✓	✓	✓	✓	✓
Vaccine administered		✓		✓						
SARS-CoV-2 IgG assessment		✓^**d**^	✓^**d**^	✓^**d**^	✓^**d**^	✓^**d**^	✓^**d**^	✓^**d**^	✓^**d**^	✓^**d**^
Blood to process and store as plasma and PBMCs^e^		✓	✓	✓	✓	✓	✓	✓	✓	✓

Notes: *M* month, *QOL* quality of life, *PBMCs* peripheral blood mononuclear cells

^a^ If randomised to a second study vaccine

^b^ If only receiving one study vaccine

^c^ Screening and baseline procedures can be completed on the same day

^d^ Quantitative ELISA for SARS-CoV-2 anti-spike IgG

^e^ Immunogenicity subset including SARS-CoV-2 neutralisation assay (see section below)

^f^ An example of an unscheduled visit is for individuals receiving anti-SARS-CoV-2 monoclonal antibodies on study and attending for additional assessment of SARS-CoV-2 IgG, ideally in the 3 days before and 3 days after the infusions to assess antibody kinetics

After receipt of each vaccine, participants will be asked to complete a survey on a secure web-based portal regarding their experience of local and systemic reactions following the trial intervention, daily for 7 days.

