## Statistical methods

### Statistical methods for primary and secondary outcomes {20a}

Baseline demographic and anthropometric data as well as the defined safety and immunogenicity outcome measures will be stratified by study cohort (HIV, SOT, haematological malignancy) and summarised with appropriate measures of spread. Immune responses and reactogenicity to COVID-19 vaccines will be assessed on a modified intention-to-treat population, depending on actual intervention received between randomisation and providing blood samples for the primary endpoint. Participants with SARS-CoV-2 infection or antibody therapy (e.g. IVIG), between randomisation and providing blood samples will be excluded from the primary analysis. For safety reporting, participants will be included in the intervention group that they received, irrespective of the intervention they were randomised to.

The primary outcome will be the anti-spike IgG antibody against SARS-CoV-2, 21–35 days after completion of study vaccines, summarised as the GMC. Participants who miss a study blood draw, have SARS-COV-2 infection diagnosed by RAT, PCR or anti-nucleocapsid antibodies, or obtain an unscheduled dose of COVID-19 vaccine between the time of randomisation and the primary endpoint will be excluded from analysis. A Bayesian hierarchical two-part model will be used for the primary analysis as it is anticipated that a significant proportion of primary outcomes may be below the assay limit of detection.

Secondary endpoints described above will be analysed depending on the type of outcome; continuous immunological variables will be modelled with the two-part Bayesian model described; binary endpoints, including safety endpoints, will be analysed using a Bayesian logistic model; a Bayesian Poisson regression will be used to compare counts and rates. Further statistical detail is available in the statistical appendix which will be published separately.

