### Adverse event reporting and harms {22}

This study will collect data on both solicited and unexpected adverse events (AE) following study intervention. At each contact with the participant, information will be sought on adverse events and details recorded in the eCRF. Solicited AEs are those events specifically captured in the diary card up to 7 days after each vaccination and for this study include pain, induration, erythema, temperature, headache, fatigue, chills, myalgia, joint pain, nausea, diarrhoea, chest pain.

Serious adverse event (SAE) is one which is deemed medically significant; warrants hospitalisation or emergency department presentation; results in congenital anomaly or permanent disability or incapacitation; and is life-threatening or causes death. SAEs are monitored continuously and have special reporting in the eCRF, and to the study sponsor and HREC within 24 h of an investigator becoming aware. All SAEs that occur from randomisation up to 28 days following the last dose of an investigational product will be documented and reported; SAEs that occur thereafter will only be documented and reported if they are deemed to be at least possibly related to the study vaccine. Suspected unexpected serious adverse reactions (SUSARs) are any SAE that is both suspected to be related to the trial treatment and is unexpected (i.e. not consistent with the available safety information in the investigator’s brochure (for unapproved products)/approved product information. A specific list of adverse events, and adverse events of special interest are defined and will be recorded if occurring throughout the course of the study for participants [39].

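### The 7-day bar on other vaccines is justified by avoiding misattributed reactions, but same-day vaccination is exempt, so the rule misses its purpose for systemic reactions (minor)

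*Protocol article*

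**What the plan says.** The protocol article's section on concomitant care {11d} contains both halves of the rule. It first gives the permission: "Participants may receive another licensed vaccine (e.g. influenza vaccine) in the opposite upper limb, concurrent with their trial vaccine". It then says that the other vaccine "cannot be administered in the period 7 days before or 7 days after the COVID-19 vaccine, to avoid misattribution of reactogenicity". No other reason for the 7-day bar is given. Eligibility criteria {10} repeats the exemption: "note: participants can receive another licensed vaccine on the same day as the COVID-19 vaccine".

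Reactions are collected by diary. Below Table 1, in Participant timeline {13}, participants are to report "regarding their experience of local and systemic reactions following the trial intervention, daily for 7 days", after each vaccine. Adverse event reporting {22} lists the solicited events, which "include pain, induration, erythema, temperature, headache, fatigue, chills, myalgia, joint pain, nausea, diarrhoea, chest pain". Local and systemic reactions on days 1 to 7 are a secondary safety outcome in Outcomes {12}, and the abstract counts them among the key secondary outcomes. On analysis, Statistical methods {20a} says that "binary endpoints, including safety endpoints, will be analysed using a Bayesian logistic model" and defers further detail to a statistical appendix that is not shown.

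**The concern.** The bar has one declared purpose, to keep reactions to another vaccine from being counted against the study vaccine. The exempted day is the one on which that confusion is greatest. The opposite-limb rule is a real safeguard for a sore or red arm, but a fever or headache has no limb.

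The objectives {7} include confirming safety, and absolute systemic reaction rates are what readers will take from the trial on tolerability. If some doses were given with, say, an influenza vaccine (the article's own example), the reported rate is that of the study vaccine plus whatever was given with it, and a reader told about the 7-day bar would not expect that.

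**Working it through.** The article states no figure for this point, so there is none to reproduce. The check has two parts.

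**1. Does the rule meet its purpose?**

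Suppose, for illustration, that reactions to the other vaccine last 7 days, the length of the diary. If it is given *k* days before or after the study dose, the number of diary days that overlap is 7 − *k*.

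- *k* = 7 (barred): 0 days overlap.
- *k* = 1 (barred): 6 days overlap.
- *k* = 0 (permitted): all 7 days overlap.

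The permitted case therefore has more overlap than any barred one.

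Of the 12 solicited events, three (pain, induration, erythema) are injection-site events that the opposite limb can separate. The other nine (temperature, headache, fatigue, chills, myalgia, joint pain, nausea, diarrhoea, chest pain) cannot be assigned to a limb.

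**2. How large could the effect be?**

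All three inputs are assumptions; none is in the article.

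- *p*: probability of a systemic reaction from the study vaccine
- *q*: probability that the other vaccine alone causes one, independently
- *c*: share of doses co-administered

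Observed rate = *p* + *c*(1 − *p*)*q*, so the excess is *c*(1 − *p*)*q*. With *p* = 0.40:

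| *c* | *q* = 0.10 | *q* = 0.20 |
|---|---|---|
| 0.10 | 0.10 × 0.60 × 0.10 = 0.6 points | 1.2 points |
| 0.25 | 1.5 points | 3.0 points |
| 0.40 | 2.4 points | 0.40 × 0.60 × 0.20 = 4.8 points |

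Over wider ranges (*p* 0.30-0.70, *q* 0.10-0.30, *c* 0.05-0.50):

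- The smallest excess is 0.05 × 0.30 × 0.10 = 0.15 points.
- The largest is 0.50 × 0.70 × 0.30 = 10.5 points, which takes a 30% rate to 40.5%.

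**Effect on comparisons between vaccines.** If *c* and *q* are the same in both arms, the observed rate is *p*(1 − *cq*) + *cq*, so a true risk difference is multiplied by (1 − *cq*):

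- *c* = 0.1, *q* = 0.1: 0.99
- *c* = 0.3, *q* = 0.2: 0.94
- *c* = 0.5, *q* = 0.3: 0.85

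A chance imbalance of 10 points in *c* with *p* = 0.50 would create a spurious difference of 0.10 × 0.50 × 0.20 = 1.0 point, or 1.5 points at *q* = 0.30. Randomisation makes the expected imbalance zero at the first dose.

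**The case against.** The strongest reply is that this is a rule with an openly stated exception. The permission comes first, the bar follows, the eligibility note repeats the exception, and the discussion calls the design pragmatic. A site can follow both rules at once, and no figures conflict. A same-day vaccine is also tied to a known visit date, whereas one given on day 3 would fall in mid-diary. All of this stands. It shows that the exemption is deliberate, but not that the stated reason is met for systemic events.

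Three stronger readings are tempting, and the article does not support them.

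- *A reader might infer that comparisons between vaccines are biased.* Allocation is central and random ({16a}), and participants and their clinicians are blinded at the first dose ({16b}, {17a}). Co-administration is therefore balanced in expectation between concurrently randomised vaccines. What remains is mild dilution and chance imbalance.
- *A reader might infer that differences between dose 1 and dose 2, or between vaccines open in different periods, will reflect influenza season.* Either could happen, but the article states no such safety contrast. Outcomes {12} anchors the reaction outcome to days 1 to 7 after randomisation.
- *A reader might infer that co-administration is neither recorded nor analysed.* The case report form and statistical appendix are not shown, and a condensed article commonly leaves such details to them. Their absence here is no finding.

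Restricting the main summary to doses given alone is also open to objection. It would replace reactions as delivered under permitted care with a different question. At the second dose (day 84), participants may already have looked up their vaccine, since the register upload is at 6 weeks ({17a}). The choice to take another vaccine that day could then depend on allocation, and the restriction could introduce selection.

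**Conclusion.** The point holds in limited form. The rationale given for the 7-day bar applies most strongly on the one day that is exempt, and the opposite-limb rule closes the gap for injection-site events only. For co-administered doses, systemic reactions cannot be attributed to the study vaccine, and absolute systemic rates are inflated to the extent that the other vaccine causes such reactions.

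The size is unknown because the article gives no share of co-administered doses. The 0.6 to 4.8 points rests wholly on the assumed 40%, 10-20% and 10-40%, and on independence of the two vaccines' reactions. If few doses are co-administered, the effect is negligible.

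Severity is minor. The point affects the interpretation of absolute rates for one secondary safety outcome.

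**What to change.** 1. Reconcile the same-day permission with the stated rationale in {10} and {11d}, for instance by saying that the misattribution rationale does not extend to systemic reactions after a same-day vaccine. This needs no change to who may be vaccinated, and no view is taken here on whether co-administration should be allowed.
2. Identify for each study dose whether another vaccine was given that day and which one, if the case report form does not already do so.
3. Keep the all-doses reactogenicity summary as the main one. Beside it, show systemic reactions separately for doses given alone and doses co-administered.
4. As a sensitivity analysis, add a dose-level co-administration term to the Bayesian logistic model for reactogenicity.

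The cost is at most one field per dose, one split table and one model term. The split table has smaller denominators. Its contrast between doses given alone and co-administered is not randomised, especially at dose 2, so it should be labelled descriptive.
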